### Eligibility criteria

Women who meet the following study inclusion criteria will be enrolled: (1) singleton pregnancy; (2) 5–12^+6^ weeks pregnancy; (3) ≥1 risk factor for GDM (e.g., maternal age ≥ 35 years old, pre-pregnancy BMI ≥ 24 kg/m^2^, family history of type 2 diabetes, polycystic ovary syndrome, previous macrosomia, previous GDM, previous glucose intolerance, previous fetal anomaly or hydramnion, current pregnancy with fetus growing greater than the gestational age, hydramnion, or repeated colitis).

Women will be excluded from this study if they have an exercise contraindication [18], such as severe cardiac or respiratory diseases, severe preeclampsia, uncontrolled hypertension, thyroid disease, type 1 diabetes, cervical insufficiency, persistent vaginal bleeding, threatened prematurity, placenta previa, ruptured membranes, poorly controlled anemia, fetal growth restriction, multiple pregnancies (≥ 3), bone or joint problems, severe obesity (body mass index > 35 kg/m^2^); are participating in other antenatal PA programs; or are currently being treated with metformin or corticosteroids.

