**Secondary outcomes**								
PA self-efficacy (P-ESES)	√	√	√	√	√	√		
Gestational weight gain (questionnaire)	√	√	√	√	√	√		
Maternal outcomes (medical records)					√	√		
Neonatal outcomes (medical records)							√	√

*Abbreviations*: *CG* Control group, *GDM* Gestational diabetes mellitus, *IG* Intervention group, *OGTT* Oral glucose tolerance test, *P-ESES* Pregnancy Exercise Self-efficacy Scale, *PA* Physical activity, *PPAQ* Pregnancy Physical Activity Questionnaire

According to the guidelines for the management of gestational diabetes mellitus in China [48], pregnant women with a fasting glucose level of ≥ 7.0 mmol/L or random blood glucose level of ≥ 11.0 mmol/L in early pregnancy are diagnosed with pre-gestational diabetes mellitus. Women who are not diagnosed with pre-gestational diabetes mellitus will receive a 75-g oral glucose tolerance test at 24–28 weeks’ gestation. Using the criteria of the International Association of Diabetes and Pregnancy Study Groups, GDM will be diagnosed when the fasting plasma glucose value is greater than the following standards: 5.1 mmol/L, 10.0 mmol/L in 1 h, or 8.5 mmol/L in 2 h [49].

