Gestational weight gain (GWG) will be calculated as the difference between weight measured at the time of inclusion, 24–28 weeks’ gestation, and 35-37 weeks’ gestation. pre-gestational BMI will be calculated using the self-reported pre-pregnancy weight and height [weight (kg)/(height (m))^2^]. According to the Working Group on Obesity in China [55], individuals may be classified as underweight (BMI < 18.5 kg/m^2^), normal weight (BMI 18.5–23.9 kg/m^2^), overweight (BMI 24.0–27.9 kg/m^2^), or obese (BMI ≥ 28 kg/m^2^) according to their BMI. We will measure maternal body weight to the nearest 0.1 kg with a calibrated electronic scale (RGZ-50; SUHONG Medical Instrument, Jiangsu, China) with participants wearing indoor clothing and no shoes. Excessive gestational weight gain will be identified according to the 2009 guideline issued by the Institute of Medicine [56]. GWG will be categorized as inadequate, normal, or excessive GWG by the same guidelines [56]. Here, inadequate GWG will be defined as a bodyweight gain < 11.5 kg for normal-weight women, < 7 kg for overweight women, or < 5 kg for obese women; normal GWG will be defined as a bodyweight gain of 11.5–16 kg for normal-weight women, 7–11.5 kg for overweight women, or 5–9 kg for obese women; and excessive GWG will be defined as a bodyweight gain > 16 kg for normal-weight women, > 11.5 kg for overweight women, or > 9 kg for obese women, respectively.

Maternal outcomes will include gestational hypertension (defined as a blood-pressure elevation [systolic blood pressure > 140 mmHg or diastolic blood pressure > 90 mmHg] at > 20 weeks’ gestation in the absence of proteinuria) [57], preeclampsia (presence of both high blood pressure and proteinuria at 20 weeks’ gestation), premature rupture of membranes (rupture of membranes before 37 weeks’ gestation or at the onset of delivery), postpartum hemorrhage (blood loss > 500 mL within 24 h of delivery), and mode of delivery (vaginal, operative vaginal, or cesarean [elective or emergency]).

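### Weight gain is measured over part of pregnancy but sorted by one fixed set of kilogram limits, with no interval named and no limits for underweight women

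*Protocol article*

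**What the plan says.** The section on outcome measures and data collection states that GWG "will be calculated as the difference between weight measured at the time of inclusion" and the weights taken at 24–28 and 35–37 weeks. Under the eligibility criteria, inclusion is at 5 to 12+6 weeks. Table 4 shows GWG at booking, 24–28 weeks and 35–37 weeks, with no entry after delivery.

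On classification, the same section states that "GWG will be categorized as inadequate, normal, or excessive GWG by the same guidelines", meaning the 2009 Institute of Medicine guideline, and gives the limits outright: "inadequate GWG will be defined as a bodyweight gain < 11.5 kg for normal-weight women, < 7 kg for overweight women" and below 5 kg for obese women. The normal bands are 11.5–16, 7–11.5 and 5–9 kg, and anything above them is excessive.

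Pre-pregnancy weight is collected but serves only to assign the BMI class: "pre-gestational BMI will be calculated using the self-reported pre-pregnancy weight and height". Four BMI classes are defined, including underweight (below 18.5 kg/m²). Limits are given for the other three.

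**The concern.** The article gives the weighing times and the limits in full, and they do not fit together. A fixed kilogram limit belongs to a particular stretch of pregnancy. Here the stretch varies from woman to woman, and the text does not say whether the 24–28 week gain, the 35–37 week gain or both are classified. Followed as written, a woman's category depends partly on when she enrolled and when she was last weighed.

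Underweight women can enrol: one risk factor suffices (age 35 or over, or a family history, for example), and the only BMI exclusion is above 35. They cannot be classified, so they would either drop out of an analysis described as intention-to-treat or be placed by an ad hoc rule.

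GWG is a named secondary outcome and appears among the aims in the conclusion. The discussion says a positive effect on any primary or secondary outcome should lead to the programme being considered for regular care, so the definition matters.

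**Working it through.** The protocol gives no misclassification figure to reproduce. The check is how much of a total gain the measured interval captures, and what that does to the categories.

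**Inputs from the protocol.** Inclusion at 5 to 12+6 weeks (12+6 = 12.86 weeks); last weighing at 35–37 weeks; limits for normal-weight women of 11.5 and 16 kg; a 40-week delivery, used in the background section as the example for counting antenatal visits.

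**Length of the interval, inclusion to last weighing.**
- Shortest: 35 − 12.86 = 22.1 weeks.
- Longest: 37 − 5 = 32 weeks.

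**Assumptions, not in the protocol.** The limits refer to whole-pregnancy gain. There is no gain before week 13 and linear gain from week 13 to week 40 (27 weeks). Total gain in normal-weight women is N(13.75, 4) kg, centred on the middle of the 11.5–16 band.

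**Share captured, f.**
- Weighed at 35 weeks: f = (35 − 13)/27 = 0.815.
- Weighed at 37 weeks: f = (37 − 13)/27 = 0.889.

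**A woman with a mid-band total of 13.75 kg.**
- At 35 weeks: 13.75 × 0.815 = 11.2 kg, classed as inadequate.
- At 37 weeks: 13.75 × 0.889 = 12.2 kg, classed as normal.

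The omitted gain is about 1.5 to 2.5 kg (13.75 × 3/27 and 13.75 × 5/27), against a band 16 − 11.5 = 4.5 kg wide.

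**Total gain needed to be called excessive (16/f).** 16/0.889 = 18.0 kg at 37 weeks; 16/0.815 = 19.6 kg at 35 weeks.

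**Category split, % inadequate / normal / excessive.** Observed gain is N(f × mean, f × SD), cut at 11.5 and 16 kg.

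| Assumed total gain | True split | Weighed at 37 weeks | Weighed at 35 weeks |
|---|---|---|---|
| N(13.75, 4) | 28.7 / 42.6 / 28.7 | 42.0 / 43.6 / 14.4 | 53.6 / 39.3 / 7.1 |
| N(13.75, 5) | 32.6 / 34.7 / 32.6 | 43.5 / 36.7 / 19.8 | 52.9 / 35.1 / 12.0 |
| N(16, 5) | 18.4 / 31.6 / 50.0 | 27.0 / 38.5 / 34.5 | 35.3 / 41.3 / 23.4 |

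A harsher assumption, linear gain over weeks 0–40, captures 32/40 = 0.80 to 22.1/40 = 0.55 of the total. The N(13.75, 4) split then becomes 56.2 / 37.9 / 5.9 for the longest interval and 96.0 / 3.9 / 0.0 for the shortest. The direction is the same in every case; the size is not.

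**Sensitivity to a difference between arms.** Keep the first pattern and let the intervention mean be 1.5 kg lower (12.25 kg, an illustration). The proportion with excessive gain is P(total > 16/f).
- True: 28.7% v 17.4%, a difference of 11.3 points.
- Weighed at 37 weeks: 14.4% v 7.5%, a difference of 6.9 points.
- Weighed at 35 weeks: 7.1% v 3.2%, a difference of 3.8 points after rounding (0.0706 − 0.0324).

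**If the limits were applied at 24–28 weeks.** f = 11/27 = 0.41 to 15/27 = 0.56. Under N(13.75, 4), 96% to 100% of normal-weight women would be called inadequate.

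**The case against.** The strongest reply is that the premise comes from outside the document. The text does not call the limits whole-pregnancy totals; it gives limits for GWG by pre-pregnancy BMI class and cites a guideline that is not shown. That is right, so the direction and size above are conditional on that reading. One point does not depend on it: a single unadjusted limit cannot suit intervals running from 22.1 to 32 weeks, whichever period it was written for.

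A reader might infer that the limits are also applied to the 24–28 week gain. The protocol does not say so; the interval is simply not named.

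A reader might also take the spread in interval length (32/22.1 = 1.45, or 45%) as a 45% spread in gain. It is a spread in weeks between two extreme cases. If little is gained before week 13, the captured share varies only from 0.815 to 0.889, about 9% in relative terms (0.889/0.815 = 1.09).

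The loss can also be smaller than shown. Under the same pattern, a woman weighed at 37 weeks who delivers at 38 has (37 − 13)/(38 − 13) = 0.96 of her gain captured. Weight loss before inclusion would offset part of the omission.

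Finally, inclusion to 35–37 weeks spans nearly all of the intervention and starts from a scale weight, so it is a defensible measure of gain under treatment. That stands, and it supports the continuous measure. It does not support the fixed categories.

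**Conclusion.** The point holds for the derived categories of one secondary outcome. The classified interval is unnamed, the limits are not matched to gestational age at weighing, and eligible underweight women have no category. If the limits mean whole-pregnancy gain, the milder pattern with N(13.75, 4) lowers excessive gain from 29% to 7–14% and raises inadequate gain from 29% to 42–54% in normal-weight women. These figures rest on the assumed gain pattern, the assumed distribution and a 40-week delivery.

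It would be tempting to call this a biased comparison. The documents do not support that: both arms are randomised 1:1 and weighed on the same schedule. The harm is wrong proportions and reduced sensitivity to a difference in excessive gain. The change in kilograms does not use the limits and is unaffected. The number of underweight women is not given and may be small.

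Table 4 lists "Gestational weight gain (questionnaire" as the source, while the text describes a calibrated scale read to 0.1 kg. The questionnaire may be only the form on which the weight is recorded, so this is editorial.

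**What to change.** 1. Make the continuous change from inclusion to 35–37 weeks the main GWG analysis, adjusted for gestational age at both weighings.
2. Use the categories only for a gain whose start and end match the limits: pre-pregnancy weight, already collected, to the last recorded weight before delivery, if the record holds one. Alternatively, use limits scaled to gestational age at weighing. State the interval, and do not apply the fixed limits to the 24–28 week gain.
3. Add limits for underweight women from the cited guideline. Its figures are not in the document, so none are suggested here.
4. Reconcile the data source in Table 4 with the scale measurement in the text.

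The first, third and fourth changes affect wording and analysis only. The second may need one more value per woman, and the protocol does not show that the medical record contains it. A category built on pre-pregnancy weight relies on self-report, and one that ends at delivery depends on gestational length, which is itself a trial outcome. Keeping the continuous change as the main analysis limits both drawbacks. Randomisation and sample size are not touched.

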A pragmatic parallel, randomized controlled trial was designed to investigate the effect of a self-efficacy-enhancing PA intervention on the incidence of GDM, blood sugar values, and PA level. The secondary objectives of this study are to investigate the effect of the PA program on PA self-efficacy; gestational weight gain; maternal outcomes, such as gestational hypertension, preeclampsia, and mode of delivery; and neonatal outcomes, including gestational age at delivery, preterm birth, Apgar score, birth weight, birth length, macrosomia, low birth weight, fetal distress, amniotic fluid contamination, number of large for gestational age (LGA) infants, and number of small for gestational age (SGA) infants.

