### Sample size

The sample size of this study was calculated based on recent research available on the impact of PA on the incidence of GDM in Chinese overweight and obese pregnant women. Using information from that study [38] documenting incidence rates of GDM of 22% in the intervention group after PA intervention and 40.6% in the control group, we found that a sample size of a ≥ 98 women in each arm of this study will be required to detect a difference in the incidence of GDM between groups (80% power and *α* = 0.05). The treatment and control ratio is 1:1. Allowing for 20% attrition during pregnancy, ≥ 122 women in each arm will need to be recruited.

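### Preeclampsia is defined by signs at 20 weeks rather than after 20 weeks, so hypertension and proteinuria first found together later meet neither of the two hypertensive secondary outcomes.

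*Protocol article*

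**What the plan says.** The Background lists the secondary maternal outcomes: "maternal outcomes, such as gestational hypertension, preeclampsia, and mode of delivery". The section Outcome measures and data collection then defines them.

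- **Gestational hypertension:** systolic pressure above 140 mmHg or diastolic above 90 mmHg, "at > 20 weeks’ gestation in the absence of proteinuria".
- **Preeclampsia:** "preeclampsia (presence of both high blood pressure and proteinuria at 20 weeks’ gestation".

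Table 4 takes maternal outcomes from medical records and ticks them only in the 35–37 week column. The column for the first 3 days after delivery is ticked for neonatal outcomes only. Study design, Treatment and assessment schedule, and Table 4 place assessments at booking, about 24–28 weeks, 35–37 weeks and within 3 days after delivery. None is at 20 weeks.

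Eligibility criteria excludes women with exercise contraindications, "such as severe cardiac or respiratory diseases, severe preeclampsia, uncontrolled hypertension, thyroid disease, type 1 diabetes" among others. Controlled chronic hypertension is not named.

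**The concern.** The two outcomes should divide hypertension arising in the second half of pregnancy by whether proteinuria is present. For that they need the same time window. One is open-ended after 20 weeks; the other, as written, is fixed at 20 weeks. Cases with both signs that first appear later then have no category, and cases that progress stay in the milder one.

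At stake is whether the two counts mean what their labels say. The Discussion states that a positive effect on any primary or secondary outcome should lead to considering the program for regular care, so a misdefined secondary outcome could enter that argument.

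**Working it through.** **The plan's own figure.** The only calculated figure is the sample size, based on "incidence rates of GDM of 22% in the intervention group after PA intervention and 40.6% in the control group", 80% power, α = 0.05 and 1:1 allocation. With a pooled-variance, two-sided comparison of proportions:

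- d = 0.406 − 0.22 = 0.186; mean proportion = (0.22 + 0.406)/2 = 0.313
- n = [1.960 × √(2 × 0.313 × 0.687) + 0.842 × √(0.22 × 0.78 + 0.406 × 0.594)]² / 0.186² ≈ 96.4, that is 97 per arm, against 98 stated
- Attrition: 98/0.80 = 122.5, against 122 stated

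The figure reproduces to within one woman. It rests on the incidence of GDM, so the definitions at issue here do not enter it.

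**Applying the two definitions as written.** No arithmetic applies. The test is to take possible courses and read each rule literally.

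| Course | Gestational hypertension? | Preeclampsia? | Result |
|---|---|---|---|
| Raised pressure and proteinuria first found together at, say, 34 weeks | No: proteinuria is present | No: not at 20 weeks | Counted in neither |
| Raised pressure without proteinuria at 28 weeks, proteinuria added at 34 weeks | Yes, at 28 weeks | No: not at 20 weeks | Counted only as gestational hypertension |
| Chronic hypertension, above 140 or 90 mmHg after 20 weeks, no proteinuria | Yes: normal pressure before 20 weeks is not required | No | Pre-existing condition counted as an event |
| Chronic hypertension, not above 140 or 90 mmHg after 20 weeks | No: threshold not crossed | No | Not counted |

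The first two rows follow from the timing of preeclampsia. The third follows from the absence of a new-onset condition, together with an exclusion list that names only uncontrolled hypertension.

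**Checking against the schedule.** With no assessment at 20 weeks, the literal definition points to a time at which the trial itself collects nothing. Table 4 has a related gap. Its single tick for maternal outcomes, at 35–37 weeks, precedes most deliveries. Hypertensive disease arising between that point and birth would not be captured at that time. Two other outcomes in the same group, mode of delivery and postpartum hemorrhage, cannot be known before birth at all. The tick is therefore inconsistent with the list of maternal outcomes as well.

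**The case against.** The strongest reply is that this is a slip of the pen. A missing greater-than sign or the word after is the natural explanation, the absence of a 20-week visit supports it, and someone abstracting records would probably apply the usual meaning. That is plausible, and it rules out a stronger inference a reader might draw: that the preeclampsia count will be near zero whatever the intervention does. The document does not show that the rule would be applied literally. What remains is that this is the only operational definition given, that other greater-than signs in the same sentence are intact, and that no other section corrects it.

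Three further readings go beyond the text.

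- A reader might infer that every case of preeclampsia after 20 weeks is lost. Only cases in which both signs are first found together fall through; those with an earlier proteinuria-free elevation after 20 weeks are misclassified.
- A reader might infer that controlled chronic hypertension is itself an outcome event. It counts only if pressure exceeds 140 or 90 mmHg after 20 weeks.
- A reader might put a number on this. An assumed prevalence of 1–4% would give 122 × 0.01 = 1.2 to 122 × 0.04 = 4.9 women per arm. The document gives no such prevalence, and the range counts every controlled hypertensive woman as crossing the threshold, so even on that assumption it is an upper bound.

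The new-onset point also has fair answers. The label gestational implies it, the definition cites a source not at hand, the list of contraindications is illustrative, and randomization should balance pre-existing hypertension between arms in expectation. The likely effect is dilution rather than bias. This keeps it a minor point.

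**Conclusion.** The preeclampsia definition is wrong as written and inconsistent with the definition beside it. Followed literally, it leaves concurrent-onset cases after 20 weeks in neither outcome and places progressing cases in gestational hypertension only. The missing new-onset condition is a smaller defect of the same text.

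The size cannot be stated: the document gives no expected incidence of preeclampsia or gestational hypertension and no prevalence of chronic hypertension. The conclusion assumes only that the published definitions govern abstraction from the records. The consequences are confined to two secondary outcomes. It should be corrected, but it does not threaten the trial's main comparison.

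**What to change.** 1. Define preeclampsia as high blood pressure with proteinuria first found after 20 weeks' gestation. State whether a woman who first meets gestational hypertension and later develops proteinuria is counted under preeclampsia only or under both.
2. Add new-onset to the gestational hypertension definition. This resolves the chronic hypertension point in the outcome wording, without any change to eligibility.
3. Align Table 4 so that maternal outcomes are abstracted from the records through the existing follow-up within 3 days after delivery, not only at 35–37 weeks.

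The cost is a few words in two definitions and one change to Table 4. Neonatal outcomes are already taken from medical records at the post-delivery follow-up, so no new visit is needed. Applying the new-onset condition needs hypertension status before 20 weeks to be identifiable from the booking data or records. Because the outcomes come from records, the corrected rules can be applied to every participant, including those already enrolled. The change should be reported to the investigators, ethics committees and registry, as the article promises for any protocol change.

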### Outcome measures and data collection

The list of data-collection instruments and times of data collection are presented in Table 4. The primary outcomes of this study are blood sugar values during the 75-g oral glucose tolerance test, the incidence of GDM at 24–28 weeks’ gestation, and PA levels at 24–28 and 35–37 weeks’ gestation. The secondary outcomes include PA self-efficacy, gestational weight gain, maternal outcomes, and childbirth outcomes.

**Table 4 Tab4:** Data collection instruments and time of data collection

	Booking		24–28 weeks’ gestation		35-37 weeks’ gestation		Within 3 days after delivery	
	IG	CG	IG	CG	IG	CG	IG	CG

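### The stated definition of premature rupture of membranes leaves out whether rupture came before labour, so applying it as written would misclassify cases of this secondary outcome

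*Protocol article*

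**What the plan says.** The section on outcome measures sets the hierarchy: "The secondary outcomes include PA self-efficacy, gestational weight gain, maternal outcomes, and childbirth outcomes". The maternal outcomes are then listed with their definitions, and the third of the five is "premature rupture of membranes (rupture of membranes before 37 weeks’ gestation or at the onset of delivery".

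The article defines this outcome nowhere else. The secondary objectives at the end of the Background refer to "maternal outcomes, such as gestational hypertension, preeclampsia, and mode of delivery"; rupture of membranes is not among those examples. Table 4 gives the data source as "Maternal outcomes (medical records").

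The next paragraph of the same section lists the neonatal outcomes. Preterm birth is one of them, defined only by delivery before 37 completed weeks.

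**The concern.** The definition joins two conditions with an or. The first depends on gestational age alone and says nothing about labour. The second places rupture at the start of delivery, not before it, and has no gestational limit. The property that makes a rupture premature in the sense of the name, that it precedes labour, is required by neither.

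The neighbouring outcomes in the same sentence, such as gestational hypertension and postpartum hemorrhage, carry explicit working criteria. A reader will therefore take this parenthesis as the rule by which cases are scored.

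What is at stake is the validity of one secondary comparison. If the rule is applied, both arms gain women who do not have the named condition and lose some who do, and the contrast between arms is blurred. The Discussion gives secondary outcomes some weight: it says that a positive effect on any outcome, primary or secondary, would be a reason to consider adding the programme to regular care.

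**Working it through.** No published figure is at issue, so the check is one of logic. The stated rule is applied to every combination of gestation and timing of rupture, and the result is compared with what the name denotes (rupture before labour starts). One assumption is needed: the onset of delivery is taken to mean the onset of labour, since the article does not define it.

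| Gestation at rupture | Timing of rupture | Counted by the stated rule | Rupture before labour |
|---|---|---|---|
| <37 weeks | before onset | yes | yes |
| <37 weeks | at onset | yes | no |
| <37 weeks | after onset | yes | no |
| ≥37 weeks | before onset | no | yes |
| ≥37 weeks | at onset | yes | no |
| ≥37 weeks | after onset | no | no |

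- The rule and the name agree in two of the six cells: <37 weeks before onset, and ≥37 weeks after onset.
- They disagree in four. Three are over-counts (<37 weeks at onset, <37 weeks after onset, ≥37 weeks at onset). One is an omission (≥37 weeks before onset).
- At 37 weeks or later the rule is the reverse of the name for the two cells that matter: it takes in rupture at onset and leaves out rupture before it.

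These are counts of cells, not of women. They show the kinds of misclassification, not how often each occurs.

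**Overlap with preterm birth.** A woman in established preterm labour whose membranes rupture during that labour, and who delivers before 37 weeks, is an event under both outcomes. The two are not the same: preterm birth is scored by gestation at delivery, whatever the timing of rupture.

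**Alternative readings**, put through the same grid:

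- *A slip for rupture before the onset of delivery.* The two cells at ≥37 weeks come right. The two over-counts below 37 weeks remain, because that part is still not tied to labour: two cells disagree.
- *The word before governs both parts, but rupture at onset is kept.* The omission at ≥37 weeks is repaired, but rupture at onset is still counted there: three cells disagree.
- *Delivery announced by rupture of the membranes.* Pre-labour rupture at term could then be counted, but the part below 37 weeks is unchanged, so the same two over-counts remain.

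**Effect on the comparison.** The rule is the same in both arms. If the wrongly counted ruptures are unaffected by the programme, they add the same expected frequency to each arm, and the omitted cases remove real contrast. Both tend to dilute a difference. To put a number on this one would need the frequency of each cell, and the article gives none.

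**The case against.** The strongest reply is that the sentence is compressed and probably a slip. One word may be misplaced, and a clinician would read it as intended. That is a fair account of how the wording may have arisen, and it counts against reading it as a deliberate choice. It does not make the stated rule correct: none of the more generous readings above brings all six cells into line, and the text does not say which was meant.

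A second reply is that the data come from medical records. If abstractors simply transcribe the recorded diagnosis, the parenthesis may never be used to score anyone. This stands in part, since the article does not say whether rupture times will be re-scored against the definition. A reader might infer that the trial's counts are bound to disagree with the recorded diagnoses; the documents do not support that. If the diagnosis is transcribed, however, the published definition misdescribes the data, and the sentence still needs correcting.

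A third reply concerns importance, and it stands. This is one of five maternal outcomes, beside eleven neonatal ones, self-efficacy and weight gain. It is not a primary outcome, and the sample size rests on something else: "incidence rates of GDM of 22% in the intervention group after PA intervention and 40.6% in the control group".

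Three stronger inferences are tempting and unsupported. That most true cases would be lost cannot be said without rates of rupture timing. That the outcome duplicates preterm birth goes too far; it overlaps with it. That the trial's safety assessment is compromised does not follow either, because the article nowhere names this as a safety outcome.

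**Conclusion.** Wrong as written, minor importance. As it stands, the definition omits the feature that gives the outcome its name. Taken literally, it counts rupture at the start of delivery at any gestation and every rupture before 37 weeks, and it leaves out pre-labour rupture from 37 weeks on. Applying it would misclassify cases in both arms.

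The conclusion rests on the article's wording and on taking the onset of delivery as the onset of labour. The expectation of dilution rests further on the rule being applied as a scoring rule, and on the wrongly counted ruptures being unaffected by the programme. Its size is unknown. The primary results and the sample size are not affected.

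**What to change.** Before records are abstracted, redefine the outcome as rupture of membranes before the onset of labour, at any gestational age. Delete the part that refers to the start of delivery. Report separately the subset in which rupture occurs before 37 weeks; this subset will still overlap with preterm birth, but each outcome will then have its own clear meaning.

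State also whether cases are scored from recorded times of rupture and labour or taken from the recorded diagnosis. If any records have already been abstracted, re-score them in both arms by the revised rule, without reference to allocation.

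The cost is one sentence in the protocol and a matching field on the extraction form. The items needed (gestational age, and whether rupture preceded labour) should be in the delivery record. The article already provides for notifying the investigators, ethics committees and registry of protocol changes, so no new procedure is needed.
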